### Power analysis

In line with the findings from De Marco et al. (2017), where increased DMN resting-state connectivity was observed in patients assigned to the experimental condition in a midline cluster extending to the precuneus and cuneus, we aim to detect similar changes in brain functional connectivity through our study. De Marco et al. reported decreased connectivity in the right and left parietal cortices for the control condition. The experimental condition showed an average increase of 0.18 z scores, while the control condition exhibited an average decrease of 0.63 z scores (mixed-design ANOVA’s F1, 35 = 15.08, *p* < 0.001). Based on these findings, we conducted a power analysis to determine the necessary sample size for detecting differences in functional connectivity changes between the experimental and control groups. Assuming a medium effect size (Cohen’s *d* = 0.5), a significance level of 0.05, and a power of 0.90, our analysis indicated that a total sample size of approximately 80 participants (40 per condition, evaluated at two time points for NBCT) would be sufficient to detect medium to large effects, ensuring robust and reliable results.

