The first TR approach is the Network-based Cognitive Training (NBCT), a cognitive training specifically designed to promote the co-activation of multiple brain areas (i.e., central nodes), modulating the functional connectivity of specific resting state networks (RSNs). This rehabilitation package has been used in face-to-face mode on a sample of healthy participants, in whom a rehabilitation-induced “up-regulation” effect of functional connectivity of the rear central nodes of the default mode network (DMN) was observed (De Marco et al., 2017). Subsequently, this training approach has been tested in amnestic MCI (De Marco et al., 2018), PD with MCI (Venneri et al., 2021) and in patients with relapsing–remitting multiple sclerosis who complained of mild cognitive deficits (Manca et al., 2021). Notably, the NBCT program will be implemented on a TR platform (i.e., Khymeia) and can be administered through a virtual connection. A link will be provided for each rehabilitation session, and this allows participants to access and use the TR protocol through a web browser on their personal computer, tablet, or mobile phone. This approach offers many advantages in terms of practicality, ease of use and accessibility for study participants.

The second TR approach is the Home-based Cognitive Rehabilitation (HomeCoRe) system. This is a software for cognitive TR especially developed for the initial stages of decline (amnestic MCI, MCI-PD, mild AD). HomeCore has been developed starting from a validated in-person computer-based cognitive intervention (CoRe) the efficacy of which in the short and long term has been verified in outpatients’ hospital services also in combination with neuromodulatory techniques (Alloni et al., 2017, 2018; Bernini et al., 2019, 2021, 2023; Rodella et al., 2022). HomeCoRe is an adaptive patient-tailored treatment focused on training memory and logical-executive functions that provides a Weighted Score of performance for each exercise and each session to monitor patients’ progress remotely and to adjust automatically the level of exercise difficulty accordingly. This strategy is applied to avoid either over- or under-stimulating patients. The software provides an easy-to -access platform that patients interact with via a touch screen. Usability and acceptance of HomeCoRe have already been tested in a small group of patients with MCI due to a neurodegenerative disease (Bernini et al., 2023).

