### Planned analysis

#### Primary outcome analysis plan

Brain connectivity measures will be extracted from both rs-fMRI and HD-EEG data. The RSNs will be constructed considering a predetermined set of seed regions (Franco et al., 2013). As we will, for the first time, investigate the efficacy of three distinct TR approaches and their associated neural correlates, we will examine brain connectivity across all major RSNs.

For rs-fMRI seed-based timecourses will be extracted from each seed region, and individual maps of functional connectivity will be computed modeling the linear association between the timecourse of the seed and the timecourse of each voxel within the identified RSNs. For HD-EEG data, brain connectivity will be extracted by assessing the weighted Phase Lag Index (wPLI) (Vinck et al., 2011) that measures the phase synchronization of two signals. For both methods, the strength of the relationship between nodes of RSNs will be quantified using seed-based analysis, estimating pairwise correlations between a seed region and all the other voxels across the brain.

We will assess if the TR intervention has effects on changes in functional connectivity between T0 and T1 and whether these effects are absent at T0 vs. T1 in the control stimulation. This approach enhances the validity of the analyses by specifically addressing the impact of the treatment on connectivity changes over time and comparing them with a control condition.

Using the formula (Δ connectivity change = T1 − T0), the changes in Pearson’s correlation coefficient transformed into z-scores will be computed for each participant within each network. A large Δ connectivity change will represent a higher correlation coefficient (stronger connectivity) at T1 than T0.

The effect of the cognitive training program on network connectivity will be tested using mixed-design full-factorial scripts modeling the condition-by-timepoint interaction (increases Δ connectivity change seen in the experimental condition net of the increases seen in the control condition). We will also test the “inverse interaction” contrast (exclusive increases in Δ connectivity change seen in the control condition) as a methodological control. The statistical model will be run independently for each considered TR approach (i.e., NBCT, HomeCoRe, and SMRT).

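### Forty per arm gives about 60% power at d = 0.5, not the stated 90%; 90% would need 86 per arm (172 in total)

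*Protocol article*

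**What the plan says.** The Power analysis section sets out to "determine the necessary sample size for detecting differences in functional connectivity changes between the experimental and control groups". Its inputs are given in one sentence: "Assuming a medium effect size (Cohen’s *d* = 0.5), a significance level of 0.05, and a power of 0.90". Its conclusion is that "a total sample size of approximately 80 participants (40 per condition, evaluated at two time points for NBCT) would be sufficient", and it goes on to describe results for medium to large effects as robust. It does not name the test, the sidedness of alpha, the SD that scales d, or a T0–T1 correlation.

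The Primary outcome analysis plan tests the training effect with "mixed-design full-factorial scripts modeling the condition-by-timepoint interaction" and adds: "The statistical model will be run independently for each considered TR approach (i.e., NBCT, HomeCoRe, and SMRT". Table 1 puts 40 participants on NBCT and 40 on its own control, with 5 and 5 for HomeCoRe and 10 and 10 for SMRT. The NBCT test therefore rests on 40 against 40; the other 30 participants do not contribute to it.

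The section takes its lead from an earlier trial of the same training (+0.18 versus −0.63 z, F(1,35) = 15.08) and calls that trial's participants patients. Citing the same trial, the Introduction says: "This rehabilitation package has been used in face-to-face mode on a sample of healthy participants".

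**The concern.** A two-group comparison at d = 0.5 with 90% power is a standard calculation, and its answer is roughly twice the number given. This paragraph is the protocol's only sample-size justification, and it covers the only comparison of any size. If the stated power is wrong, ethics committees and readers are told that the trial can reliably detect a medium effect when it cannot. A null NBCT result would then be read as evidence against a medium effect that the trial had a substantial chance of missing.

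**Working it through.** **Inputs.** d = 0.5, alpha = 0.05, power = 0.90 and n = 40 per arm (Power analysis); 1:1 allocation (Control for confounding variables and biases); condition-by-timepoint interaction with two time points, run separately for each approach (Primary outcome analysis plan). Sidedness is not stated, so both are shown.

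**Test.** With two groups and two visits, the interaction F test is the square of the two-sample t test on change (T1 − T0). The natural reading is that d is the group difference in mean change divided by the SD of change.

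**Sample size for 90% power.** Normal approximation, two-sided:

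n per arm = 2(1.960 + 1.282)² / 0.5² = 84.1, so 85.

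The noncentral t gives 85.03, so 86 per arm (85 gives 89.99%), 172 in total. One-sided it gives 69.2, so 70 per arm. The stated 40 is not reproduced. Lowering the target to 80% power does not reproduce it either: 64 per arm two-sided, 51 one-sided.

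**Power at 40 per arm.** Noncentrality = 0.5 × √(40/2) = 2.236 on 78 degrees of freedom.

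| | Power at d = 0.5 |
|---|---|
| two-sided 0.05 | 59.8% |
| one-sided 0.05 | 71.6% |

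**Detectable effect at 40 per arm, two-sided.** d = 0.734 for 90% power and 0.634 for 80%.

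**Other routes to 80.**

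1. *Repeated-measures within–between routine with f = d/2 = 0.25.* The noncentrality is f² × 2/(1 − r) × N, where r is the T0–T1 correlation. Setting this equal to the t-test noncentrality N·d²/4 gives an implied change-score d = √(0.5/(1 − r)).

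| r | N for 90% | Power at N = 80 | Implied change-score d |
|---|---|---|---|
| 0 | 88 | 87.8% | 0.71 |
| 0.1 | 78 | 90.9% | 0.75 |
| 0.3 | 62 | 96.2% | 0.85 |
| 0.5 | 46 | 99.3% | 1.00 |

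Eighty suffices from r of about 0.1 upwards, but for non-negative r the effect being powered is never below 0.71 SD of change.

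2. *d scaled to the single-visit SD.* The change-score d is then 0.5/√(2(1 − r)). Reaching 0.734 needs r = 1 − (0.5/0.734)²/2 = 0.77. With baseline adjustment the requirement is r = √(1 − (0.5/0.734)²) = 0.73. At r = 0.5, power is 60% (change score) or 72% (baseline-adjusted).

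3. *Pre/post test within one arm.* At d = 0.5 and n = 40, power is 86.9%, and 44 per arm give 90%. This is close to the stated figures, but it is not a comparison with control.

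**Earlier trial.** Assuming two near-equal groups totalling 37 (from 35 error degrees of freedom), t = √15.08 = 3.88 and d ≈ 2 × 3.88/√37 = 1.28. Power at 40 per arm for that effect exceeds 99%, but the protocol did not size on it.

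**Loss of paired data.** Illustrative rates, not from the protocol: with 36 usable pairs per arm (10% loss) power at d = 0.5 is 55% two-sided; with 32 (20% loss) it is 50%.

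**The case against.** The strongest reply is that the article condenses a fuller calculation. It mentions two time points and plans a mixed-design analysis, so a repeated-measures routine with f = 0.25 is a plausible origin. In that routine 80 is sufficient at any correlation of about 0.1 or more, and the text claims sufficiency, not a minimum. Equally, if d was meant on the single-visit SD and connectivity is stable enough between visits, 40 per arm could reach 90%.

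Part of this stands. The 60% figure belongs to a two-sided test with d on the SD of change, and the one-sided figure is 72%. The likely fault may be a mislabelled effect size rather than a slip in calculation.

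It does not save the sentence. The section says it is powering "detecting differences in functional connectivity changes between the experimental and control groups", for which the SD of change is the natural scale, so the gain from two visits is already counted in d. The repeated-measures route makes 80 enough only by powering a larger effect than the one named. The single-visit route depends on a high correlation that appears nowhere. The covariates listed in the analysis plan do not include baseline connectivity, so the slightly easier baseline-adjusted requirement is not clearly available. Nor is this a detail left to another document: the inputs and the result are both stated here, and they disagree.

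The loss rates and the d of 1.28 rest on assumptions labelled above; the conclusion does not depend on them.

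**Conclusion.** The stated power is wrong on the stated inputs. For a between-group difference in change of d = 0.5, 40 per arm give 60% power two-sided or 72% one-sided, against 90% claimed; 90% needs 86 or 70 per arm. The chance of missing a true medium effect is therefore about 40% (28% one-sided), not 10%. This assumes d on the SD of change, complete T0 and T1 data in all 80, and a single test with no allowance for multiple networks or for clustering by centre. An undisclosed T0–T1 correlation of about 0.73 to 0.77, with d on the single-visit SD, would change the answer, but it would have to be stated and justified. The description of the earlier trial's participants as patients is a separate, smaller inconsistency with the Introduction. This must be corrected before the power claim is relied on.

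**What to change.** Keep the sample and correct the claim.

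1. State the test, the sidedness and the SD that scales d. If a T0–T1 correlation was used, give it with its source.
2. If the test is two-sided on change scores, replace the conclusion with: *With 40 evaluable participants per arm and two-sided alpha 0.05, the NBCT comparison has 90% power for a between-group difference in change of d of about 0.73, 80% power for about 0.63, and 60% power for 0.5.* If it is one-sided, say so and recompute (72% at d = 0.5; 90% for d of about 0.66).
3. Give the same figures at the number expected to have usable paired T0/T1 data.
4. Remove the closing assurance of robust results as it applies to medium effects.
5. Describe the earlier trial as one in healthy participants treated face to face, consistent with the Introduction. If an effect size is derived from its F statistic, state the group sizes used.

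The cost is wording only. No additional participants are needed, but the stated power becomes less favourable. Keeping 90% power at d = 0.5 instead would require 172 participants for NBCT alone.

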**Figure 1 fig1:**
[figure not shown]
CONSORT flow chart for enrolment and randomization.

**Table 1 tab1:** Characteristics of included interventions.

Approach	Network-Based Cognitive Training (NBCT)	Home-based Cognitive Rehabilitation (HomeCoRe)	Semantic Memory Rehabilitation Training (SMRT)	Unstructured Home-based Cognitive Stimulation (Sham Comparator)
Participants	40 participants with MCI randomly allocated to NBCT.	5 participants with MCI randomly allocated to HomeCoRe.	10 participants with MCI randomly allocated to SMRT.	55 MCI, randomly assigned to one of three control groups (CG): CG for NBCT (*n* = 40), CG for HomeCoRe (*n* = 5), CG for SMRT (*n* = 10).
Interventions	Cognitive training specifically designed to promote cognitive functions in early stages of neurodegenerative conditions.	Cognitive training specifically designed to promote cognitive functions in early stages of neurodegenerative conditions.	Cognitive training specifically designed to promote cognitive functions in early stages of neurodegenerative conditions.	This activity is commonly used as a control condition to test the efficacy of innovative rehabilitative treatments.

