### Control for confounding variables and biases

After baseline assessment, patients included in the study will be randomly allocated to two groups in a ratio of 1:1 based on active and control interventions, controlling for sex and education levels. We will generate random numbers with a computer algorithm^1^ from a uniform distribution in the range 0–1, dividing the range into two equal intervals and assigning each participant to the group corresponding to the sampled number (1,1 ratio). Stratification will be employed to ensure equal distribution of participants within each stratum (e.g., blocks based on sex and education level), and block randomization will be used within each block. Propensity score matching will be applied using logistic regression and matching participants based on similar scores, to ensure comparable groups.

Neuropsychologists carrying out cognitive evaluations will be blinded to group allocation to prevent bias. They will receive appropriate instruction and guidance regarding all assessment procedures and outcome parameters. Reminders (e.g., written reminders, phone calls, and email messages) for each visit will be sent to all participants to ensure compliance and complete data collection.

Not all outcome measures will be administered at each time point (summary in Table 2).

**Table 2 tab2:** Evaluation battery across testing sessions.

	T0	T1	T2	T3

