### Ethical issues

This trial will involve human participants, cognitive TR interventions, data collection, elaboration and abstraction used for the evaluation of two therapeutic options. In addition to ethical approval, all procedures and data management strategies have been approved by the Data Protection Officer of the University of Pavia who guarantees compliance with the GDPR (General data protection regulation). Information provided when acquiring informed consent from participants will be given in a language appropriate to the individual level of understanding. Participants will also be encouraged to ask questions before signing the informed consent form.

To the best of our estimation, TR interventions should not have any potential negative impact on the participant. Moreover, both HD-EEG and rs-fMRI are non-invasive techniques for the study of human brain function.

The investigators will communicate any possible, unforeseen, adverse event to the Ministry of Health. Regarding payment policies for participants, any compensation amount, method and timing of disbursement must be consistent with the laws, regulations, and guidelines of the region in which the study is conducted and must not improperly influence a participant’s decision to participate. This trial is a no profit study and, in Italy, the national legislation states that it is forbidden to offer or request any kind of financial benefit/incentive for participation in clinical experimental trials.

Since participants are expected to interact with a TR tool, one possible issue could be frustration in case of lack of ability to cope with that technology. However, this risk will be mitigated, before the beginning of TR treatment, thanks to specific training sessions on the use of this application that will be provided to participants (and possible caregivers). Moreover, the interface is fully compliant with the guidelines for human-computer interaction, to make the user interface as easy as possible.

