This study has some limitations that need to be acknowledged. Participants with limited computer skills and without a supportive caregiver might be excluded from using TR, introducing a selection bias in this type of intervention (Moo et al., 2020). Nevertheless, evidence suggests that telemedicine devices can be effectively used by individuals with early cognitive impairment who live alone (Smith et al., 2007). Furthermore, it should be noted that the three different TR interventions are characterized by a different overall duration and frequency of sessions, which could affect the comparability of the approaches. However, only maintaining the pre-existing characteristics of each intervention, we are able to establish their feasibility and efficacy, thus paving the way for larger confirmatory trials.

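### The NBCT sample size counts 40 per arm evaluated at both T0 and T1, but exactly 40 per arm are randomised, so the stated size leaves no room for loss and the stated effect of 0.5 is not what that number detects

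*Protocol article*

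**What the plan says.** The Power analysis is written for the NBCT comparison. Its inputs are "Assuming a medium effect size (Cohen’s *d* = 0.5") with "a significance level of 0.05, and a power of 0.90", and its result is that "a total sample size of approximately 80 participants (40 per condition, evaluated at two time points for NBCT) would be sufficient". The count is therefore of people measured at both time points.

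Table 1 gives the numbers randomised: "40 participants with MCI randomly allocated to NBCT" and, in the sham column, "CG for NBCT (*n* = 40"). The section on confounding and bias fixes the order of events: "After baseline assessment, patients included in the study will be randomly allocated to two groups in a ratio of 1:1". The T1 acquisition comes after the intervention, hence after allocation. The Primary outcome analysis plan defines the primary variable for each participant as connectivity at T1 minus connectivity at T0.

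On possible losses, the section on participant-centred outcomes plans criteria, reminders and follow-up for non-adherence. The Ethical issues section foresees frustration among people who cannot cope with the technology and answers that "this risk will be mitigated, before the beginning of TR treatment, thanks to specific training sessions on the use of this application". Neither section gives a rate, and the sample size carries no allowance.

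**The concern.** The number required with complete data and the number randomised are the same, 40 per arm. One participant without a T1 acquisition, or without a usable T0 acquisition, takes that arm below the figure on which the 90% power rests. The article states both numbers itself, so this is not a detail left to a fuller document.

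At stake is the power of the main comparison, the only one for which a sample size is justified. The effect of loss depends on how much spare power there is at 40 per arm, so the stated figure has to be checked first.

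**Working it through.** **Inputs.** d = 0.5, alpha 0.05, power 0.90 and 40 per condition (Power analysis); 40 + 40 randomised (Table 1); primary variable T1 − T0 (Primary outcome analysis plan). The article does not state sidedness, whether d refers to the change score or the raw score, or the T0–T1 correlation. I take a two-sided test and d on the change score, and vary this below. The loss rate is my assumption, 5% to 20%, equal in both arms.

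**Step 1: the plan's own figure.** For two groups compared on the change score, n per arm = 2(z₀.₉₇₅ + z₀.₉₀)²/d² = 2(1.960 + 1.282)²/0.25 = 84.1, so 85 per arm (86 with the t distribution). One-sided, it is 69 (70 with t). The stated 40 is not reproduced. With 40 per arm and d = 0.5, power from the non-central t is 60% two-sided and 72% one-sided.

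Other readings come near 40 per condition only with something the article does not state:
- Paired t test within one arm: 44 two-sided or 36 one-sided. This does not compare the arms.
- Group-by-time interaction F test with f = 0.25: 46 in total at a T0–T1 correlation of 0.5, and 88 at 0. It gives 78 to 82 only at a correlation of about 0.05 to 0.10.
- d = 0.5 on the raw score, adjusted for baseline (ANCOVA), 40 per arm: 87% power at correlation 0.70 and 92% at 0.75.
- d = 0.5 on the raw score, analysed as change: 88% at correlation 0.75 and 94% at 0.80.

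**Step 2: effect of loss.** Evaluable n per arm = 40 × (1 − loss). The detectable d solves the non-central t power equation at 90%, two-sided 0.05.

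| Assumed loss | Evaluable per arm | Detectable d at 90% power | Power at d = 0.5 | Power at d = 0.73 |
|---|---|---|---|---|
| 0% | 40 | 0.73 | 60% | 90% |
| 5% | 38 | 0.75 | 58% | 88% |
| 10% | 36 | 0.77 | 55% | 87% |
| 15% | 34 | 0.80 | 53% | 85% |
| 20% | 32 | 0.82 | 50% | 82% |

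**Step 3: numbers that would keep 40 evaluable.** n randomised = 40/(1 − loss), rounded up: 43, 45, 48 and 50 per arm at 5%, 10%, 15% and 20% loss (86, 90, 96 and 100 in total), against 40 per arm (80) planned. If the evaluable size were 86 per arm, as d = 0.5 on the change score needs, the same formula gives 91, 96, 102 and 108 per arm.

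**The case against.** The strongest reply is that little is lost. The article says approximately 80, and no trial needs every participant to complete. If 40 per arm did give 90% power, a 10% loss in both arms would cost about 3 points. Reminders, check-ins and training are planned. The earlier study cited in the Power analysis, with F(1, 35) = 15.08, implies d of about 1.28 if its arms were of nearly equal size (√15.08 × √(1/18 + 1/19)), well above 0.82. All this stands as a comment on size. It does not repair the statement, because the article plans on d = 0.5, where power is about 60% before any loss.

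Three stronger readings are tempting, and the documents do not support them.

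- **That the target cannot be met.** It can, with zero loss. The accurate statement is that there is no margin.
- **That the article predicts dropout through poor computer skills.** The Discussion says "Participants with limited computer skills and without a supportive caregiver might be excluded from using TR, introducing a selection bias". This concerns who can enter telerehabilitation, and it joins two conditions. Lack of family support is already an exclusion criterion. Trouble with the software also does not imply a missing scan, since nothing says that non-adherent participants go unscanned or leave the analysis.
- **That losses will fall more on the active arm and bias the comparison.** The tasks differ, but the control is also delivered remotely through telerehabilitation with a therapist online. No figure in the article bears on a difference, and any size put on such a bias would rest on invented inputs.

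Unusable acquisitions are likewise not mentioned in the article. They are a reasonable inference for imaging and EEG, no more.

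**Conclusion.** The concern holds in a limited form. The sample size is stated as evaluated at both time points, the same number is randomised, and no loss is allowed for. The stated basis is met only with complete data.

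The loss itself costs a modest amount: under an assumed 5% to 20%, the detectable d rises from 0.73 to between 0.75 and 0.82, and power at d = 0.5 falls from about 60% to between 58% and 50%. The larger part of the gap from the planned 0.5 exists before any loss, so inflating 40 for dropout would not by itself restore 90% power at d = 0.5. These figures assume a two-sided test at 0.05, d on the change score and equal loss in both arms. A high T0–T1 correlation, with d defined on the raw score, could justify about 40 per condition, but the article states neither.

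**What to change.** In the Power analysis:
- State the number randomised, the assumed loss rate and the expected evaluable number per arm.
- Give the detectable effect, or the power at d = 0.5, at the evaluable number. Alternatively, state the scale of d, the test and the T0–T1 correlation that would justify 40 per condition, and still apply the loss to it.

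Where feasible, confirm that the T0 acquisition is usable before allocation, so that this source of loss falls before randomisation.

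I would not add failure of technology training as an exclusion criterion. It would work against the stated aim of assessing feasibility, and training all candidates on the application before allocation would expose future controls to the active software.

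The cost is a less favourable stated figure and a short quality check before allocation. Recruitment need not change unless the sponsor chooses to keep 90% power at d = 0.5.
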